**Fig. 1 Fig1:**
[figure not shown]
Flowchart of the study design

## Randomization and blinding

Stratified block randomization will be conducted by the Chinese Academy of Chinese Medicine Sciences (CACMS) with their online central randomization system. Clinical physicians in subcenters will oversee the recruitment process. Each patient will be given a unique ID through a web interface provided by CACMS, where they will be randomly allocated to each group at a ratio of 1:1 via the central randomization system. Each trial drug will be labeled with a unique number and dispatched with the online system at each visit. All experimental drugs and corresponding placebo treatments are consistent in appearance and taste. The grouping information of each participant will be concealed to all research personnel and data analyzers until the trial ends. Unblinding will be permitted in cases of serious AEs.

## Interviews

From the first day to the observation point of week 96, we will follow up patients every 24 weeks (± 3 days) and dispatch trial drugs on each visit. In addition, we will retrieve the empty boxes and the remaining doses of each patient for verification and recording. At the end of week 96, patients will be informed again about the potential risks of stopping NA therapy, and additional consent to participate in off-therapy observation will be required. From week 96 to week 120, we will set the intervals between interviews to 4 weeks (± 3 days).

Specimens collected during the trial will be stored in the Biobank of Dongzhimen Hospital. The specimens will be used to reconfirm the readings of existing assessments if necessary, as well as for genetic or molecular analysis in current trials and for future use in ancillary studies.

## Assessments

To ensure safety and reveal the curative effects of trial drugs, patients will be monitored regularly with assessments throughout the trial (Table 1).

**Table 1 Tab1:** Scheduled assessments

Assessment	Consolidation therapy									Off-therapy observation						Treatment after recurrence
	Day 1	12 w	24 w	36 w	48 w	60 w	72 w	84 w	96 w	4 w	8 w	12 w	16 w	20 w	24 w	Recurrence
**Blood, urinary, and stool routine test**	**√**		**√**		**√**		**√**		**√**						**√**	
**Liver functions**	**√**		**√**		**√**		**√**		**√**	**√**	**√**	**√**	**√**	**√**	**√**	**√**
**Renal function**	**√**		**√**		**√**		**√**		**√**						**√**	
**HBV-serum marker**	**√**		**√**		**√**		**√**		**√**			**√**			**√**	**√**
**HBV DNA**	**√**		**√**		**√**		**√**		**√**	**√**	**√**	**√**	**√**	**√**	**√**	**√**
**Liver biopsy**	**√**								**√**							
**ccc DNA**	**√**								**√**							
**HBcrAg**	**√**		**√**		**√**		**√**		**√**			**√**			**√**	
**HBV pregenomic RNA**	**√**		**√**		**√**		**√**		**√**			**√**			**√**	
**LHBs**	**√**		**√**		**√**		**√**		**√**			**√**			**√**	
**AFP**	**√**		**√**		**√**		**√**		**√**						**√**	
**PT**										**√**	**√**	**√**	**√**	**√**	**√**	
**ECG**	**√**		**√**		**√**		**√**		**√**						**√**	
**Abdominal ultrasound scan**	**√**		**√**		**√**		**√**		**√**						**√**	
**Antibodies of hepatitis A, C, D, E**	**√**															
**CLDQ**	**√**	**√**	**√**	**√**	**√**	**√**	**√**	**√**	**√**			**√**			**√**	
**SF-36**	**√**	**√**	**√**	**√**	**√**	**√**	**√**	**√**	**√**			**√**			**√**	
**The symptom score of TCM**	**√**	**√**	**√**	**√**	**√**	**√**	**√**	**√**	**√**			**√**			**√**	

Patients will be followed up every 12 weeks during the consolidation therapy and every 4 weeks in the off-therapy observation (“w” is short for “weeks”)

*Abbreviations*: *HBV* hepatitis B virus, *ccc DNA* covalently closed circular DNA, *HBcrAg* hepatitis B core-related antigen, *LHBs* HBV large surface proteins, *AFP* alpha fetoprotein, *PT* prothrombin time, *ECG* electrocardiogram, *SF-36* the Short Form (36-item) Health Survey, *CLDQ* the Chronic Liver Disease Questionnaire

## Primary outcomes

The primary outcome will be the incidence of recurrence after ETV withdrawal. Clinical recurrence is defined as a serum aminotransferase (ALT) over twofold of the upper limit of normal (ULN) while the HBV DNA > 2000 IU/mL.

## Secondary outcomes

Secondary outcome measurements include virus serological indicators, HBV DNA, liver function, liver biopsy results, cccDNA, hepatitis B core-related antigen (HBcrAg), HBV pregenome RNA (pgRNA), HBV large surface proteins (LHBs), the symptom score of TCM, the Short Form (36-item) Health Survey (SF-36), and the Chronic Liver Disease Questionnaire (CLDQ).

## Safety monitoring

Primary vital signs and laboratory parameters will be assessed in patients regularly. Primary vital signs include body temperature, blood pressure, heart rate, and respiratory rate. Laboratory tests include routine blood, urine, and stool tests, along with fecal occult blood tests, ECG, and abdominal B ultrasound scan. In particular, relapse after drug discontinuation is defined as an HBV DNA level > 2000 IU/mL with a serum ALT > 2 × ULN.

## Adverse events

We will document and report any AEs that occur during the trial and analyze any causal relationships between such AEs and the trial drug (TGBXJD granules). If any AE occurs, the PIs will ensure that the participant receives the corresponding treatment. If a relationship between the AEs and the trial drug cannot be ruled out, the event will be reported to the ethical committee and the project supervisor to determine whether or not the treatment should be suspended for the individual.

## Statistics analysis

An independent statistical committee will be in charge of the analysis. The statistical analysis team will conduct the intention-to-treat (ITT) analysis for the primary outcome, where all randomized populations will be included in the full analysis set (FAS). Subjects who violated the protocol will be inspected individually. The last observation carried forward method will be used to impute missing data.

### Missing data

Missing data will be inspected manually; if critical assessments for judging clinical relapse are incomplete (including ALT and HBV DNA) during the off-therapy period, the case will be excluded from the primary outcome analysis. If the incomplete data only affect the secondary or safety analysis, we will impute them with the last observation carried forward method.

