## Sample size estimation

We calculated the sample size with PASS software (NCSS, LLC. Utah, USA. Version 15.0.5). Referencing a study published in 2016, in which the recurrence rate was 32% in HBeAg positive CHB patients after NA withdrawal within 24 weeks [24], we determined that we would need to achieve 80% power to detect a difference between the group proportions of 12%. The required significance level was set to 0.05. We set the sample size to 245 for each group, 490 in total, for which a 20% loss of participants was considered.

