### Outcome analysis

For the primary outcome, the proportions of patients who developed off-therapy relapse in each group will be compared with the Pearson chi-square method. Time to event analysis will be performed with the Kaplan-Meier method. For the secondary outcomes, the data are continuous variables, for which we will use repeated-measures mixed effects models to test differences between the groups. The total effect of the scale scores from questionnaires will be tested with the Wilcoxon rank sum test. A paired *t* test will be used for comparisons of data before and after treatment within groups. A two-sided *p* value < 0.05 will be considered statistically significant; confidence intervals (CIs) are set at 95%.

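### The primary outcome has two incompatible rules: intention-to-treat on all randomised patients with LOCF, and exclusion of patients with incomplete off-therapy ALT or HBV DNA

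*Protocol article*

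**What the plan says.** The Statistics analysis section commits the primary outcome to intention-to-treat, "where all randomized populations will be included in the full analysis set (FAS"). It adds, with no outcome excepted: "The last observation carried forward method will be used to impute missing data".

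The Missing data section, directly below, takes the tests needed to judge clinical relapse (ALT and HBV DNA). If they are incomplete "during the off-therapy period, the case will be excluded from the primary outcome analysis". It keeps LOCF for gaps that touch only secondary or safety analyses.

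Outcome analysis compares the proportions with off-therapy relapse by Pearson chi-square and adds: "Time to event analysis will be performed with the Kaplan-Meier method".

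Three other provisions decide who has off-therapy data at all. Under Therapeutic regimen, patients with clinical relapse during the 96 weeks are removed from the study, and stopping ETV requires persistently normal ALT and undetectable HBV DNA. Under Interviews, a further consent is needed at week 96 before off-therapy observation.

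**The concern.** A randomised patient without usable off-therapy ALT and HBV DNA is in the primary analysis under one section and out of it under the next. The denominator, both recurrence rates and possibly the significance of the result depend on which sentence the analyst follows, and that choice could be made after the data are seen. The article fixes both rules for the primary outcome, so this is not a detail left to an analysis plan.

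The group affected is built into the design. Patients removed for on-therapy relapse, those who do not meet the withdrawal criteria and those who decline the second consent may have no off-therapy measurements. These filters act after randomisation, over up to 96 weeks of randomised treatment, so they can be related to prognosis and can differ between arms.

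**Working it through.** **Inputs from the article.** Sample size estimation gives "the recurrence rate was 32% in HBeAg positive CHB patients after NA withdrawal within 24 weeks", and "we would need to achieve 80% power to detect a difference between the group proportions of 12" percentage points, read here as 32% versus 20%. It also states "The required significance level was set to 0.05", and Outcome analysis makes this two-sided: "A two-sided *p* value < 0.05 will be considered statistically significant". The size is 245 per group, with a 20% loss considered. Table 1 has six off-therapy visits with liver function and HBV DNA.

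**The plan's own figure.** With mean proportion 0.26, the pooled two-proportion formula gives

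n = [1.960·√(2·0.26·0.74) + 0.842·√(0.32·0.68 + 0.20·0.80)]² / 0.12² = (1.2158 + 0.5172)² / 0.0144 = 208.6, so 209 per group.

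209 × 1.20 = 251, within 3% of 245 (unpooled: 206 × 1.20 = 248). So 245 is approximately reproduced with multiplicative inflation; 209 / 0.80 = 262 does not match. With all 245 per group observed, power for 32% versus 20% is 86.0%.

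**The rules side by side.**

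| Randomised patient | Statistics analysis | Missing data |
|---|---|---|
| No off-therapy ALT/HBV DNA | In, value carried forward | Out |
| Off-therapy ALT/HBV DNA incomplete | In, value carried forward | Out |
| Gap affects secondary or safety data only | LOCF | LOCF |

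They agree only where the primary outcome is not involved.

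**LOCF applied to the primary outcome.** A patient who stops ETV under the withdrawal criteria and is lost before the first off-therapy visit carries forward normal ALT and undetectable HBV DNA, and counts as recurrence-free. A patient lost later carries the last off-therapy value. If a share m is lost before any recurrence is seen, equally in both arms and regardless of who would have recurred, the observed rate is p(1 − m). The article gives only the 20% loss allowance, so m is an assumption:

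| m | Control | Experimental | Difference (points) | Power at 245 per arm |
|---|---|---|---|---|
| 5% | 30.4% | 19.0% | 11.4 | 83.5% |
| 10% | 28.8% | 18.0% | 10.8 | 80.8% |
| 20% | 25.6% | 16.0% | 9.6 | 74.6% |
| 30% | 22.4% | 14.0% | 8.4 | 67.4% |

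For m = 20%: the null standard error is √(2·0.208·0.792/245) = 0.03667 and the alternative one is √[(0.256·0.744 + 0.16·0.84)/245] = 0.03641. Power = Φ[(0.096 − 1.960·0.03667)/0.03641] = Φ(0.663) = 74.6%.

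**Exclusion.** With a share r missing among recurrers and s among non-recurrers, the complete-case rate is p(1 − r) / [p(1 − r) + (1 − p)(1 − s)]. The values of r and s are assumptions:

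| r | s | Control | Experimental | Difference (points) |
|---|---|---|---|---|
| 20% | 20% | 32.0% | 20.0% | 12.0 |
| 30% | 15% | 0.224/0.802 = 27.9% | 0.140/0.820 = 17.1% | 10.9 |
| 40% | 10% | 0.192/0.804 = 23.9% | 0.120/0.840 = 14.3% | 9.6 |
| 10% | 25% | 0.288/0.798 = 36.1% | 0.180/0.780 = 23.1% | 13.0 |

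In the first row there is no bias, only loss of size: 245 × 0.80 = 196 per arm. Power = Φ[(0.12 − 1.960·0.04431)/0.04389] = Φ(0.755) = 77.5%. The other rows move the rates down or up.

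**The case against.** The best defence is that the Missing data section is the specific rule and narrows the general LOCF sentence, so LOCF never reaches the primary outcome. That is a fair reading, and under it the LOCF table describes a rule that is not used. It does not rescue the plan: leaving cases out of the primary analysis still contradicts including all randomised patients.

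Several stronger inferences are tempting, and the article does not support them.

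- *Both rules necessarily bias the result.* Exclusion does so only if missingness is related to recurrence, and then in either direction.
- *Any difference in drop-out between arms passes straight into the treatment effect.* Under exclusion, unequal loss unrelated to recurrence within each arm leaves the proportions unbiased. The inference fits LOCF only: with a true 32% in both arms and 15% versus 25% lost, LOCF gives 27.2% versus 24.0%.
- *One missed visit of six excludes a patient.* With an assumed independent 5% miss rate per visit that would remove 1 − 0.95⁶ = 26%. But the article does not define incomplete, and gaps are inspected manually.
- *A documented early relapse would be dropped.* The rule concerns tests needed to judge relapse, a confirmed relapse has been judged, and Table 1 schedules both tests at recurrence. The wording should still say so.
- *Patients with a flare seek treatment elsewhere.* Nothing in the article says this; retreatment is provided within the trial.

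It is also fair that a 20% loss was already considered, so the fall to 77.5% power under random exclusion is modest.

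**Conclusion.** The point stands: the two sections define incompatible primary analyses, and one must give way. This rests on the text alone. On the most charitable reading the primary analysis is complete-case, contrary to the stated intention-to-treat.

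The size of any bias cannot be known from the article. The figures above assume true rates of 32% and 20% and a chosen level and pattern of loss. They show that the choice of rule can matter: at 20% loss, a 9.6-point difference and 74.6% power under LOCF, against an unbiased 12 points and 77.5% power under exclusion at random, or a shift either way if exclusion is related to recurrence. The post-randomisation filters make that last case a real risk, not an established fact. Because the primary denominator is at stake and the repair is cheap, it should be made before unblinding.

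**What to change.** 1. Delete the sentence in Missing data that excludes cases from the primary analysis, and state in Statistics analysis that LOCF does not apply to the primary outcome.
2. Keep all randomised patients in the primary comparison of proportions. Count any documented recurrence as an event, whatever visits are missed later.
3. Multiply impute recurrence status where it is unknown, and state the imputation assumption.
4. State explicitly how randomised patients who never enter the off-therapy phase are counted: those removed for on-therapy relapse, those not meeting the withdrawal criteria and those declining the second consent. Censoring them at time zero would be exclusion under another name.
5. Keep the Kaplan-Meier analysis as supportive, censored at the last complete ALT/HBV DNA pair, and note that it assumes non-informative censoring.
6. Add a sensitivity analysis that counts missing as recurrence or applies a delta adjustment.

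The cost is a few sentences, a little more analysis work and reliance on a stated imputation assumption. No new data are needed.

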## Therapeutic regimen

Patients who meet the inclusion criteria will be allocated in a 1:1 ratio to either the experimental group (EG) or the control group (CG). Patients in the EG will receive TGBXJD granules along with ETV. Patients in the CG will receive TCM placebo along with ETV. The treatment duration is 96 weeks. Those who develop clinical relapse during consolidation therapy (in the first 96 weeks) will be switched to TDF (300 mg per day) according to the guidelines [25] and be removed from the study. All patients who meet the following NA withdrawal criteria in the first 96 weeks will stop their ETV treatment and will be closely monitored in the following 24 weeks: (1) serum ALT persistently within the normal range (under 40 IU/L) and (2) serum HBV DNA persistently undetectable (under 30 IU/mL). Once clinical recurrence is confirmed during the off-therapy period, antiviral treatment (entecavir, 0.5 mg per day) will be restarted immediately (Fig. 1).

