### Safety analysis

Safety analysis will be performed based on the subjects who actually received treatment. We will compare the data with Student’s *t* test or the Mann–Whitney *U* test. In addition, abnormal results from safety assessments will be further classified as “abnormal (no clinical significance)” and “clinically abnormal.” The latter will be inspected to determine they were caused by the trial drugs. The incidence of AEs will be described, and the specific grades of all the AEs in each group and their relationships with drugs will be described in detail. The proportions of patients who developed AEs between groups will be compared with Pearson’s chi-square test.

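### Carrying the last observation forward for missing safety tests puts Day 1 values into the week 24 comparison and on-treatment values into the off-therapy one; the effect is minor and the remedy cheap

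*Protocol article*

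**What the plan says.** Two sentences in the protocol article prescribe last observation carried forward (LOCF). Statistics analysis has a general one: "The last observation carried forward method will be used to impute missing data". Missing data has a specific one that names safety: "If the incomplete data only affect the secondary or safety analysis, we will impute them with the last observation carried forward method". The same section excludes a case from the primary analysis when off-therapy ALT or HBV DNA is incomplete, so its LOCF sentence covers patients whose relapse status can be judged.

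On the population, Safety analysis states: "Safety analysis will be performed based on the subjects who actually received treatment". It goes on to compare the data between groups by t or Mann-Whitney tests, and AE proportions by chi-square.

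Safety monitoring lists the tests concerned: "Laboratory tests include routine blood, urine, and stool tests, along with fecal occult blood tests, ECG, and abdominal B ultrasound scan". Table 1 (Assessments) gives their timing:

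- Blood, urine and stool tests, renal function, AFP, ECG and ultrasound: Day 1, weeks 24, 48, 72 and 96, then once off therapy, at off-therapy week 24 (study week 120).
- Liver function: the same on-treatment visits, and all six off-therapy visits.
- PT: the six off-therapy visits only.

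**The concern.** LOCF replaces a test that was not done with an older one and then treats it as a result for the later visit. With a 24-week schedule, the older value can belong to a different treatment state. A Day 1 value entered at week 24 describes the patient before the granules could act. A week 96 value entered at off-therapy week 24 describes the patient before withdrawal. Both would enter the group comparison as if observed.

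What is at stake is the laboratory, ECG and ultrasound evidence on a herbal add-on given for 96 weeks. A real difference between groups would look smaller than it is, and the denominators would overstate how many patients were tested.

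**Working it through.** **Inputs.** The LOCF rule is in Missing data, the tests in Safety monitoring, the visit schedule in Table 1 and the comparison in Safety analysis. Renal function and AFP are not listed under Safety monitoring; I include them because they share the same schedule and are naturally read as safety tests. That Day 1 is pre-dose is inferred. The article gives no rate of missed safety tests, so there is no figure of its own to reproduce. The 20% in Sample size estimation is a planned loss of participants, not a rate of missed tests.

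**Step 1: which patients the rule reaches.** On the strictest reading of Missing data, it reaches a patient with complete off-therapy ALT and HBV DNA who missed, say, an ECG or a renal test. The gap then affects only the safety analysis, and LOCF applies.

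**Step 2: which value is carried**, for the tests in the first Table 1 group above:

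| Missing at | Scheduled values available | State of the carried value |
|---|---|---|
| Week 24 | Day 1 | Pre-dose |
| Weeks 48, 72, 96 | Previous on-treatment visit, if done | Same phase, but older |
| Off-therapy week 24 | Week 96 or earlier | On treatment, or Day 1 |

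The first and last rows are the problem. A missing liver function result at off-therapy week 24 would normally be filled from off-therapy week 20. PT has no on-treatment value to carry.

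**Step 3: dilution at week 24.** Let δ be the true mean difference between groups at week 24 and m the share of values carried from Day 1, equal in both arms and unrelated to the result. Randomisation makes the expected Day 1 difference zero, so

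expected observed difference = (1 − m) × δ + m × 0 = (1 − m) × δ.

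- m = 2%: 0.98 δ
- m = 10%: 0.90 δ

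With an assumed δ of 0.30 SD, these are 0.98 × 0.30 = 0.294 SD and 0.90 × 0.30 = 0.270 SD. In patients, with 245 per arm, 245 × 0.02 = 4.9 and 245 × 0.10 = 24.5, so about 5 to 25 per arm. With the 196 left after the planned loss (245 × 0.80), 196 × 0.02 = 3.9 and 196 × 0.10 = 19.6, so about 4 to 20.

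**Step 4: comparison with as-observed analysis.** With N per arm and a common SD, the ratio of signal to standard error is

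- LOCF: (1 − m) δ / √(2/N), a factor of (1 − m) relative to complete data;
- as observed: δ / √(2/[N(1 − m)]), a factor of √(1 − m).

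At m = 2% the factors are 0.980 and 0.990; at m = 10% they are 0.900 and 0.949. Keeping the untested patients in therefore costs slightly more sensitivity than leaving them out, and it also biases the estimate.

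**Step 5: abnormality rates.** If only abnormalities new since Day 1 are counted, the same factor applies: assumed rates of 10% and 5% become 9% and 4.5% at m = 10%. If any abnormal value counts, an abnormal Day 1 result is carried forward too, and the direction is uncertain.

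**Step 6: off-therapy week 24.** No size can be given, because the documents support no figure for missed tests at that visit. The fault is one of kind: the carried value contains no information about the period after withdrawal.

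**The case against.** The strongest reply is that the rules on which observation may be carried, such as post-dose only or within phase only, are details an article leaves to the full protocol or SAP. That stands, and a reader should not infer that the absence of such a limit is itself an error. The finding is that the article commits in writing to imputing safety data at all.

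A second reply is that the consequences are small. AE incidence, grading and causality come from reports, clinically abnormal results are reviewed individually, and missing data are to be inspected manually. This also stands, and it sets the size of the point.

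A third is that as-observed analysis is not free of selection: patients may miss tests because they are unwell or have left. That is true, but LOCF does not cure it; it hides it behind a full denominator.

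Three stronger readings are tempting and not supported:

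- **Patients who relapse off therapy would all be filled with on-treatment values.** The "Treatment after recurrence" column of Table 1 schedules only liver function, HBV markers and HBV DNA. But Therapeutic regimen says "Once clinical recurrence is confirmed during the off-therapy period, antiviral treatment (entecavir, 0.5 mg per day) will be restarted immediately" and does not remove these patients; removal applies to relapse in the first 96 weeks. The column can equally be read as an extra visit. Nothing says that these patients miss the week 120 tests, so neither an imbalance in imputed values between groups nor an inflated false-positive rate can be derived.
- **Everyone who leaves early is filled from Day 1.** That depends on the general sentence in Statistics analysis governing safety data. It follows text on the primary outcome, so this is open and I do not count it.
- **Off-therapy safety as a whole rests on one visit.** This is untrue of liver function and PT.

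**Conclusion.** The point holds as a minor one. The article fixes LOCF for safety data, and its own schedule makes Day 1 the only source for a missing week 24 result and an on-treatment or Day 1 value the only source for a missing off-therapy week 24 result, for the tests ticked just once after withdrawal. The week 24 difference is pulled toward zero by the share carried, 2% to 10% at an assumed 2% to 10% missingness. This assumes that missed tests are equally common in both arms and unrelated to the result, and that Day 1 is pre-dose. Untested patients are counted as tested. The primary outcome, AE incidence, sample size and significance level do not change.

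**What to change.** Make two edits to the analysis section. In Missing data, delete 'or safety' from the LOCF sentence. In Statistics analysis, state that the general LOCF sentence does not apply to safety data. Then add, for example: *Safety measurements are analysed as observed, without imputation, by visit and treatment phase, with the number tested at each visit. A Day 1 value is never used as a post-dose result. Each patient's worst post-dose value is also summarised.*

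No new visits or tests are needed. The cost is that denominators vary by visit and patients who leave drop out of later summaries, which loses information if they left because of toxicity. The worst-value summary, built from data already collected, offsets this by keeping their on-treatment results in view.
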